#### Inclusion visit

The inclusion visit (which is the same as the screening visit) will include a physical examination, including cardiac blood flow, body temperature, and pain evaluation; a laboratory test battery (blood ion profile, ASAT, ALAT, total bilirubin, indirect bilirubin, alkaline phosphatase, GGT, amylase, lipase, CRP, hCG (if applicable), procalcitonin levels, and leukocyte count).

The laparoscopic appendectomy will then be performed, regardless of the hour or day, and the randomization performed after the appendectomy.

#### Follow-up visits

During hospitalization, the patient will be examined twice a day by the attending medical staff. A blood test will be performed on day one (a complete blood count, platelet count, C-reactive protein, and procalcitonin levels; Table 2, Spirit figure).

**Table 2 Tab2:** Follow-up visits (Spirit figure)

	Screening visit D−1 or D0	Inclusion D−1 or D0	Preoperative period D−1 or D0	Perioperative period	Post-operative period D1–D3	Post-operative FU call D8 post-surgery	Post-operative FU visit D15 ± 7 post- surgery	Post-operative FU visit D30 ± 7 post-surgery
Check on eligibility	✓	✓						
Informed consent		✓						
Clinical examination		✓	✓	✓				✓
Biological examination		✓	✓	✓		✓^a^		
ß-hCG test (women of child-bearing age)		✓						
Search for AEs		✓	✓	✓				✓
Surgery (laparoscopic appendectomy)				✓				
Randomization				✓				
Systematic perioperative sample				✓				
Post-operative antibiotics for 3 days					✓			
Daily follow-up visits				✓				
Post-surgery follow-up surgeon						✓	✓	✓

^a^ blood ion profile, ASAT, ALAT, total bilirubin, indirect bilirubin, alkaline phosphatase, gamma GT, amylase, lipase, CRP, beta HCG, procalcitonin and leucocyte count.

*FU* follow-up

Depending on the clinical situation and the suspected presence of infection, several scenarios are possible. Patients randomized into the antibiotic group can potentially be discharged by the surgeon after completion of the intravenous treatment on POD 4 if there is no post-operative infection. In such an event, the antibiogram will not be inspected by the surgical team. If the patient has a temperature of more than 38.5 °C (suggesting the presence of a post-operative infection), appropriate additional examinations and an antibiogram will be obtained. If a post-operative infection is confirmed and the antibiogram results are available, the antibiotic treatment will be modified. If a post-operative infection is not confirmed, other appropriate treatment will be provided (Fig. 1).

**Fig. 1 Fig1:**
[figure not shown]
Synopsis of the study

Patients randomized into the non-antibiotic group can potentially be discharged by the surgeon after completion of the intravenous placebo on POD 4 if there is no post-operative infection. If the patient has a temperature of more than 38.5 °C (suggesting the presence of a post-operative infection), appropriate additional examinations and an antibiogram will be obtained. If a post-operative infection is confirmed, an appropriate antibiotic treatment will be administered. If a post-operative infection is not confirmed, other appropriate treatment will be provided.

At the moment of discharge, patients will leave with a letter describing all the signs to monitor that should elicit the patient to seek medical care. He/she will be called by the investigating site on POD 8 to diagnose any sign of complications. Patients will be asked whether they had fever or abdominal pain and be reminded of the phone number of the hospital digestive surgery unit, as given in the discharge letter (available 24 h a day). At the postoperative follow-up visits, the investigator will check for post-operative complications. The first visit will take place 15 days after the patient’s surgery and will include a blood test (a complete blood count, platelet count, C-reactive protein, and procalcitonin levels). The second visit will take place 28 days after the patient’s surgery. During the follow-up visit, the investigator will check on the occurrence of an adverse event and (if applicable) the management of this event (hospitalization, antibiotics, radiological, or surgical drainage, etc.). The primary endpoint will be evaluated at this time.

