### Endpoints of the trial

#### Primary outcome

The primary outcome will be the proportion of patients with organ/space SSIs by postoperative day (POD) 30. Organ/space SSIs are officially defined by the CDC [23] as infections that occur within 30 days of surgery AND appear to be related to the surgery AND affect the organ or the cavity around the surgical site (i.e. any anatomical structure—other than the incision—that is opened or handled during surgery) AND for which at least one of the following signs is observed: pus coming from a drain placed in the organ or cavity, bacteria isolated from a liquid or tissue sample collected aseptically from the organ or cavity, and an abscess or other obvious sign of infection of the organ or cavity found by macroscopic examination during subsequent surgery or in a radiological or histopathological examination. Infection of the organ or cavity is diagnosed by the surgeon (or the physician attending to the patient). In the protocol, the SSI will be confirmed on a CT scan by the presence of an organ/space abscess (defined as an enwalled fluid-filled cavity in which the fluid contains gases) [24], which will be treated with antibiotics (either alone or in combination with radiological or surgical drainage, depending on the clinician’s decision).

The investigators evaluating the primary endpoint will be blinded to the treatment group.

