#### End of follow-up visit

There will be two post-operative visits, on POD 15 and one month (± 1 week) after the patient’s discharge. This visit will be performed by the investigators (and not by the patient’s general practitioner) for all included patients. Patients not seen at POD 15 and/or one month will be invited to visit the hospital. The patient’s general practitioner (who will have received a letter emphasizing the importance of the primary endpoint) will also be contacted before the patient is considered to have been lost to follow-up.

All data will be anonymized.

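### The final visit that ascertains the primary endpoint is timed in three contradictory ways, and all three allow assessment before the 30-day endpoint window has closed

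*Protocol article*

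**What the plan says.** The Primary outcome section fixes the window from surgery: "The primary outcome will be the proportion of patients with organ/space SSIs by postoperative day (POD) 30". The definition it adopts covers "infections that occur within 30 days of surgery AND appear to be related to the surgery".

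The final visit, at which this is ascertained, is then described three times:

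- **Follow-up visits, Table 2:** the last column is headed "Post-operative FU visit D30 ± 7 post-surgery".
- **Follow-up visits, text below Fig. 1:** "The second visit will take place 28 days after the patient’s surgery". The paragraph closes with "The primary endpoint will be evaluated at this time", which makes this the visit that yields the endpoint.
- **End of follow-up visit**, where the anchor changes from surgery: "There will be two post-operative visits, on POD 15 and one month (± 1 week) after the patient’s discharge".

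The earlier scheduled contacts after discharge are a phone call on POD 8 and a visit at day 15 (± 7 in Table 2). The Follow-up visits section allows discharge on POD 4 when there is no infection. The general practitioner is contacted only before a patient is declared lost to follow-up.

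**The concern.** The three statements differ in nominal day (30, 28, about 34), in anchor (surgery or discharge) and in permitted range. A site cannot tell which one governs. The only one that expressly says the primary endpoint is evaluated at the visit puts that visit before the endpoint window ends.

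A patient seen on POD 23 or POD 28 and recorded as event-free has not completed the 30 days. Such a patient has attended, so the general practitioner contact is not triggered, and no contact on or after POD 30 is described.

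The direction matters because the Analysis of the primary endpoint section uses a fixed absolute margin of 5 points. If the same share of events goes unrecorded in both arms, both rates shrink in proportion and so does any true difference between them. That moves a truly inferior strategy towards a finding of non-inferiority.

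**Working it through.** **Inputs.** From Sample size: control rate 12%, margin 5 points, two-sided alpha 5%, power 80%, loss to follow-up 10%, 738 per group (1476 in total) before the increase for interim analyses. From the sections quoted above: the three visit timings and discharge on POD 4. Assumed, not in the documents: a month of 30 days, and the share of events missed.

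**1. The plan's own figure.** Evaluable patients per arm:

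n = (1.960 + 0.842)² × 2 × 0.12 × 0.88 / 0.05² ≈ 663.1, rounded up to 664.

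664 / 0.90 = 737.8, rounded up to 738 per group, 1476 in total. This matches the plan. The point does not dispute the sample size; 664 is used below as the evaluable number per arm.

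**2. Visit windows on a common scale (POD).**

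| Source | Earliest | Nominal | Latest | Days of the window after the earliest visit |
|---|---|---|---|---|
| Table 2: 30 ± 7 from surgery | 23 | 30 | 37 | 7 |
| Text below Fig. 1: 28 from surgery | 28 | 28 | 28 | 2 (always) |
| End of follow-up visit: 4 + 30 ± 7 | 27 | 34 | 41 | 3 |

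Taking the month as 28 to 31 days moves the earliest discharge-anchored visit to between POD 25 and POD 28. With a 30-day month, that rule guarantees POD 30 or later only if discharge is on POD 7 or later (7 + 30 − 7 = 30). So all three versions allow assessment before POD 30, and adopting any one of them unchanged would not cure the problem.

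**3. Other scheduled contacts.** The call is on POD 8, and the day-15 visit falls at the latest on POD 15 + 7 = 22. Neither covers the end of the window.

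**4. Illustration of the effect.** Suppose a share f of events is missed equally in both arms and the true rates sit at the margin, 12% versus 17%. The observed rates are 0.12(1 − f) and 0.17(1 − f), so the observed difference is 0.05(1 − f). With SE the unpooled standard error at n = 664 per arm:

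P(non-inferiority declared) = Φ{[0.05 − 0.05(1 − f)] / SE − 1.96}

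| f (assumed) | Observed rates | Difference (points) | P(non-inferiority declared) |
|---|---|---|---|
| 0 | 12.0% vs 17.0% | 5.00 | 2.5% |
| 2% | 11.76% vs 16.66% | 4.90 | 2.8% |
| 5% | 11.4% vs 16.15% | 4.75 | 3.4% |
| 10% | 10.8% vs 15.3% | 4.50 | 4.6% |

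When the true rates are equal, a common loss leaves the expected difference at zero.

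**The case against.** The strongest reply is that this is a wording inconsistency with little practical effect, because late events would reach the database by other routes. Ethical considerations lists surgical site infection among the serious adverse events to be notified and followed up. Every patient leaves with a letter of warning signs and a 24-hour number. Rehospitalization and post-operative infections by POD 30 are recorded outcomes. The endpoint itself is a CT-confirmed, treated abscess, which normally brings a patient to care. An event is therefore lost only if it arises after the visit and also escapes these routes. This stands as mitigation. It does not close the gap, because the routes rely on the patient presenting and on the event being reported back, and no contact on or after POD 30 is stated.

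The missed shares have no source in the documents. That also stands. For scale, even a constant daily risk with no other reporting would put 2/30 = 6.7% of events after a POD 28 visit, so the 10% row exceeds what the 28-day rule alone could produce under that assumption. The 7-day gap is the edge of a window centred on day 30.

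Three stronger readings are tempting but are not supported:

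- **That the three timings exclude each other.** They overlap. A visit on POD 28 satisfies all three when discharge is on POD 4. They are contradictory as specifications, not impossible to meet together.
- **That the discharge anchor biases the endpoint by observing patients with long stays for longer.** The endpoint is capped at 30 days from surgery, so later observation adds no countable events. Only assessment before POD 30 matters.
- **That the analysis could not remove the resulting bias.** Counting by onset date disposes of events after POD 30. Randomization is stratified by center, and patients and endpoint evaluators are blinded, so differences in visit day between sites should balance across arms. The documents show no mechanism for a difference between arms.

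It might also be said that a condensed article leaves scoring rules to the full protocol or analysis plan. That is fair for the scoring details. It does not excuse three conflicting timings that the article itself states.

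**Conclusion.** The point holds as a contradiction in how the primary endpoint is ascertained, and it should be fixed. Two things follow from the text alone: the final visit has three conflicting timings, and each permits assessment before POD 30 (the discharge-anchored one when discharge is before POD 7, with a 30-day month). The part of the window without a scheduled contact is always 2 days under the 28-day rule, up to 7 under Table 2, and up to 3 under the discharge rule with discharge on POD 4.

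The number of events lost cannot be derived, because the documents give no distribution of SSI onset times. It may be small. The rise from 2.5% to about 2.8%, 3.4% or 4.6% depends on assumed equal losses of 2%, 5% or 10% and a true difference exactly at the margin. It shows the direction and rough scale and is not an estimate for this trial.

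**What to change.** Give the final assessment one definition and use it in Table 2, in the text below Fig. 1 and in the End of follow-up visit section:

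- Anchor it on surgery and hold it on or after POD 30, for example day 30 to day 37. Remove the 28-day and the discharge-anchored wording.
- Record the onset date, and count every organ/space SSI with onset up to POD 30, whenever it is reported.
- If a patient is seen earlier, make a phone contact on or after POD 30 before scoring that patient as event-free.

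The cost is a wording amendment, a one-sided visit window that is somewhat less convenient for sites, and some extra calls. The sample size, margin and treatment do not change.

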#### End of follow-up visit

There will be two post-operative visits, on POD 15 and one month (± 1 week) after the patient’s discharge. This visit will be performed by the investigators (and not by the patient’s general practitioner) for all included patients. Patients not seen at POD 15 and/or one month will be invited to visit the hospital. The patient’s general practitioner (who will have received a letter emphasizing the importance of the primary endpoint) will also be contacted before the patient is considered to have been lost to follow-up.

All data will be anonymized.

#### Cessation rules

All patients will be free to withdraw their consent and ask to be withdrawn from the study at any time and for any reason. In the event of premature withdrawal, the investigating physician must specify the reason as fully as possible.

The investigating physician will be able to withdraw a patient for any reason that might harm the patient (especially the presence of an adverse event).

The study may be stopped in the event of unexpected serious adverse events or new information suggesting that the study’s objectives will not be reached, as decided by the sponsor. A data safety monitoring board (DSMB) has been nominated (including a biostatistician, a surgeon, an infectious disease specialist, and an anesthesiologist). There will be a meeting after the first ten inclusions (in case of an adverse event), every 100 inclusions, and at the interim analysis. The DSMB has the power to stop the study.

### Randomization

An interactive web response system will be used to randomize patients using a randomization list with blocks of equal size (with the same number of randomized patients in each group, i.e., antibiotics vs no antibiotics) and stratified by center.

At the end of the surgery, investigators will check the inclusion and non-inclusion criteria. If the patient meets all of the inclusion criteria and none of the non-inclusion criteria, the investigators will log him/her into the electronic case report form and request that a treatment number be allocated to the patient.

The sequence of the study treatments (preoperative and perioperative antibiotic therapy, laparoscopic appendectomy, with or without post-operative antibiotic therapy) will be generated by a data manager using a computer program. The allocation of patients to the different study groups will involve the use of a secure, independent computer to ensure that the investigator cannot interfere with the results of this procedure. Randomization (1:1) will be stratified by center.

Randomization will be performed by an identified investigator. At the end of the surgery, the investigator will log onto the study web site (https://recherche-clinique.chu-amiens.fr/csonline/) using his/her personal username and password. The patient will be registered online and a participant number will be allocated. If the patient satisfies the inclusion/exclusion criteria and stratification criteria, he/she will be randomized, and the investigator will gain access to the treatment number allocated to the patient.

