Complicated appendicitis is defined as perforated appendicitis, extraluminal fecaliths, an abscess, or local or generalized peritonitis [8]. The definition of localized peritonitis is controversial in terms of the macroscopic aspect of the liquid (from serosity to pus) and the number of quadrants contaminated by pus. It is therefore easier to first define uncomplicated appendicitis (i.e., catarrhal appendicitis without any liquid in the abdomen) and then define complicated appendicitis as any appendicitis that is not uncomplicated. In a recent report on a randomized, controlled trial in children, St Peter et al. defined complicated appendicitis as appendicitis with a hole in the appendix or with fecaliths; they excluded abscesses and local peritonitis from the definition, because the latter conditions were surprisingly associated with a lower rate of post-operative complications than the former (14% vs 18%) [8]. Nevertheless, the study of St Peter et al. is the only one to have specified the nature of complicated appendicitis. All other studies have referred to “complicated appendicitis” without providing any details. More recently, a group at Saint-Antoine Hospital developed a predictive score for CAA (without defining CAA). It is based on five factors (a body mass index (BMI) < 28 kg/m^2^, a leukocyte count < 15,000/ml, a serum C-reactive protein (CRP) level < 30 mg/l, an appendix diameter of 10 mm or less, and the absence of radiological signs of perforation). The likelihood of CAA (ranging from 0% with a score of 5 to 100% with a score of 0) can therefore be used to preoperatively identify patients with CAA [9]. The highest risk for CAA was associated with a Saint-Antoine score ≤ 3. In the present study, we define cases of CAA as patients with a preoperative Saint-Antoine score ≤ 3 that are perioperatively confirmed by the presence of a perforated appendix, extraluminal fecaliths, abscesses, and/or localized peritonitis (pus in one or two abdominal quadrants), according to a recent study of our group [10]. In this study, we found a concordance between surgeons in 85% of cases for the definition of a CAA and the type of CAA (localized or generalized peritonitis) and two quadrants was the best cut-off between localized and generalized peritonitis by receiver operating characteristic (ROC) curve analysis [10]. We have used this definition (two or less quadrants with pus) to define localized peritonitis.

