### Blinding method

This will be a double-blind study. In the post-operative period, patients will receive either the antibiotic therapy (ceftriaxone-metronidazole or levofloxacin-metronidazole) or the placebo. Both will be injected intravenously for 3 days. The placebo will be formulated in the same format as the antibiotics. The investigators evaluating the primary endpoint will be blinded to the treatment group, as well as the included patients. The nurses who perform the injection will not be blinded. The vigilance unit must have a copy of the randomization list or a set of envelopes for unblinding.

Unblinding will be performed by the vigilance unit if the occurrence of an unexpected serious adverse effect (SAE) is suspected before declaration to the competent health authorities and annually when annual safety reports are drafted*.*

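### Center-stratified blocks of one size, with unblinded nurses and a late judgement of eligibility, leave allocation open to prediction if past allocations leak; varied block sizes and an eligibility lock are a cheap improvement

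*Protocol article*

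**What the plan says.** All references are to the protocol article.

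- **Block scheme (Randomization).** The list is a "randomization list with blocks of equal size", with equal numbers per arm in each block. "Randomization (1:1) will be stratified by center". The block length is not given.
- **Timing (Randomization).** "At the end of the surgery, investigators will check the inclusion and non-inclusion criteria", and the allocation request follows at once. "Randomization will be performed by an identified investigator"; the text does not say that this is the operating surgeon.
- **Safeguard (Randomization).** Allocation runs on a secure, independent computer "to ensure that the investigator cannot interfere with the results of this procedure". What is released is a number, not an arm: "the investigator will gain access to the treatment number allocated to the patient".
- **Who knows the arm (Blinding method; Discussion).** "The nurses who perform the injection will not be blinded". The Discussion adds that blinding the nurses proved unworkable, and that patients and surgeons are to stay blinded.
- **Room for judgement (Inclusion criteria; Appendicitis).** The article concedes that localized complicated appendicitis has no official definition. It relies on a two-quadrant rule and a training video. On agreement it reports: "we found a concordance between surgeons in 85% of cases for the definition of a CAA", and the same figure covers the type of complicated appendicitis.

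**The concern.** Three stated features combine. Blocks of one length within a center make the end of each block deducible for anyone who knows the earlier allocations and the length. Some site staff know the arms of the patients they treat. The last eligibility decision leaves room for judgement and comes directly before allocation.

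The secure computer and the treatment number protect the list itself. They do not stop someone inferring the next allocation from the previous ones. An investigator who expected placebo next could judge a borderline patient to have generalized peritonitis and not randomize. If such patients carry a higher risk of organ/space infection, withholding them from the placebo arm alone would lower its rate and move the comparison toward non-inferiority.

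**Working it through.** **1. The plan's own figure.** With 12% in both arms, a 5-point margin, one-sided 2.5% and 80% power:

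n = (1.960 + 0.842)² × 2 × 0.12 × 0.88 / 0.05² = 663.1, so 664 per arm. Then 664 / 0.90 = 737.8, so 738 per arm and 1476 in total.

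This matches the Sample size section. The point does not depend on it; it supplies the 664 evaluable patients per arm used in step 5.

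**2. Predictability with one block size.** Assume every past allocation at the center and the block size are known. For a balanced block of 2k patients, the share of allocations at which only one arm remains is 1/(k + 1). Full enumeration also gives the success rate of the best guess (50% with no information).

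| Block size (assumed) | Known with certainty | Best guess correct |
|---|---|---|
| 4 | 33.3% | 70.8% |
| 6 | 25.0% | 68.3% |
| 8 | 20.0% | 66.6% |

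**3. Bias from acting on certain predictions only.** Let f be the certain share and p the borderline share. If every borderline patient is withheld when placebo is certain, the placebo rate falls by f × p × (r_high − r_low). Illustrative assumptions, not from the article: p = 15%, risk ratio 1.5 or 2. The overall rate of 12% is the plan's.

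- Ratio 1.5: r_low = 0.12 / (0.85 + 0.15 × 1.5) = 11.16%, r_high = 16.74%, p × difference = 0.837 points. Times f: 0.28, 0.21 and 0.17 points for sizes 4, 6 and 8.
- Ratio 2: r_low = 0.12 / (0.85 + 0.15 × 2) = 10.43%, r_high = 20.87%, p × difference = 1.565 points. Times f: 0.52, 0.39 and 0.31 points.

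**4. Acting on best guesses as well.** If borderline patients are withheld whenever placebo is the likelier arm, some are wrongly withheld from antibiotic slots. With g the best-guess rate, f is replaced by the net share 2g − 1: 0.417, 0.367 and 0.332 for sizes 4, 6 and 8. The bias becomes 0.35, 0.31 and 0.28 points (ratio 1.5), or 0.65, 0.57 and 0.52 points (ratio 2). The figures in step 3 are therefore not a strict ceiling.

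**5. Against sampling error.** At the margin (17% against 12%, 664 per arm) the standard error is √[(0.17 × 0.83 + 0.12 × 0.88) / 664] = 1.93 points. A shift of 0.17 to 0.52 points, carried over unchanged, would raise the one-sided error from 2.5% to about 3.1% to 4.6%, and only if the full mechanism operated at every center.

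**6. What varied blocks would change.** Simulation of 40 patients per center, 2000 runs, with past allocations and candidate sizes known:

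| Scheme | Certain | Best guess correct |
|---|---|---|
| Fixed 4 | 33.3% | 70.8% |
| Random 4/6 | 5.7% | 68.9% |
| Random 4/6/8 | 2.5% | 67.5% |

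Certain predictions nearly vanish. Best-guess success barely moves, because it comes mainly from knowing past allocations.

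**The case against.** The strongest reply is that the decisive link is missing. The article says that nurses know the arm; it does not say that enrolling staff learn it. Surgeons are meant to be blinded and the investigator receives only a number. Exploiting the blocks would take disclosure of earlier allocations, a running tally, a known or inferred block length, and deliberate misclassification. This stands: the article describes an opening, not an event.

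The block wording could also be read as meaning only balanced blocks. But the parenthesis after it states the balance separately, so one constant length is the plain reading. The length may be in the full protocol, and its absence here is not a fault.

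Three stronger inferences are tempting and are not supported:

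- **That selection would leave no trace.** Consent and baseline blood tests precede surgery, and copies of consent forms go to the sponsor. A patient withheld afterwards is a consented, non-randomized patient, and baseline severity can be compared between arms. What does hold is narrower: the center table described under Data collected and follow-up covers only patients who meet the criteria, so the reason for a late exclusion would be hard to audit from it.
- **That 85% concordance means 15% of patients are borderline at two quadrants.** The figure covers both the definition and the type of complicated appendicitis, and the Discussion describes it as agreement with the initial operative report. It shows that judgement varies. It does not size the borderline group.
- **That borderline patients have 1.5 to 2 times the risk.** Nothing in the article supports this. The one comparison within complicated disease that it quotes, from a pediatric trial, gives 14% for abscess or local peritonitis against 18% for the other forms, and it does not test the two-quadrant boundary.

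It is also fair that the investigator already checks criteria and enters the patient in the electronic form before requesting a number. The article does not say that findings are locked at that point, or entered for patients judged ineligible.

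**Conclusion.** The point holds as a conditional weakness in a stated design choice, worth correcting because correction is cheap. On the plain reading the blocks are all of one size within center. If past allocations leak and the size is known or inferred, 33%, 25% or 20% of allocations are certain for sizes 4, 6 and 8.

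Under the illustrative assumptions, acting on those predictions would shift the result by about 0.2 to 0.5 points toward non-inferiority; acting on best guesses too could reach about 0.65. Both are small against the 5-point margin, and partial leakage would make them smaller. They rest on an assumed block size, an assumed borderline share and risk ratio, and full leakage with the same behavior at every center. The article does not support a claim that concealment has failed or that the trial result would be materially biased.

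**What to change.** 1. In the Randomization section, replace the equal-size blocks with block sizes that vary at random within center and are not disclosed to sites.
2. Require the operative findings (quadrants with pus, perforation, extraluminal fecalith, abscess) and the eligibility verdict to be locked in the electronic case report form before a treatment number is released. Apply this also to consented patients judged ineligible, so that late exclusions can be audited.
3. In the Blinding method section, instruct the unblinded nurses not to disclose allocations to anyone who enrolls patients.

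The cost is a regenerated list, slightly looser balance in small centers and a little more data entry. The sample size does not change. The first measure alone is not enough: it removes most certain predictions, but the second and third are needed against guessing from leaked allocations.
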